# AGI grade-guided chaiqin chengqi decoction treatment for predicted moderately severe and severe acute pancreatitis (CAP trial): study protocol of a randomised, double-blind, placebo-controlled, parallel-group, pragmatic clinical trial

**DOI:** 10.1186/s13063-022-06792-x

**Published:** 2022-11-08

**Keywords:** Acute pancreatitis, Chaiqin chengqi decoction, Randomised controlled trial, Traditional Chinese medicine

## Abstract

**Background:**

Acute pancreatitis (AP) is a common digestive disease with increased incidence globally but without internationally licenced pharmacological therapy. Moderately severe and severe acute pancreatitis (MSAP/SAP) contributes predominately for its morbidities and mortality and has been managed in West China Hospital for decades using the traditional Chinese medicinal formula chaiqin chengqi decoction (CQCQD). The current study tests whether the early administration of CQCQD will result in improved clinical outcomes in predicted MSAP/SAP patients.

**Methods:**

This is a single-centre, randomised, controlled, double-blind pragmatic clinical trial. AP patients aged 18–75 admitted within 72 h of onset will be assessed at admission for enrolment. We excluded the predicted mild acute pancreatitis (Harmless Acute Pancreatitis Score > 2 at admission) and severe organ failure (Sequential Organ Failure Assessment [SOFA] score of respiratory, cardiovascular, or renal systems > 3) at admission. Eligible patients will be randomly allocated on a 1:1 basis to CQCQD or placebo control administration based on conventional therapy. The administration of CQCQD and placebo is guided by the Acute Gastrointestinal Injury grade-based algorithm. The primary outcome measure will be the duration of respiratory failure (SOFA score of respiratory system ≥ 2) within 28 days after onset. Secondary outcome measures include occurrence of new-onset any organ failure (SOFA score of respiratory, cardiovascular, or renal system ≥ 2) and new-onset persistent organ failure (organ failure lasts > 48 h), dynamic surrogate biochemical markers and clinical severity scores, gut-centred treatment modalities, local complications status, intensive care need and duration, surgical interventions, mortality, and length of hospital stay. Follow-up will be scheduled on 6, 12, and 26 weeks after enrolment to assess AP recurrence, local complications, the requirement for surgical interventions, all-cause mortality, and patient-reported outcomes.

**Discussion:**

The results of this study will provide high-quality evidence to appraise the efficacy of CQCQD for the early management of AP patients.

**Trial registration:**

Chictr.org.cn Registry (ChiCTR2000034325). Registered on 2 July, 2020.

**Supplementary Information:**

The online version contains supplementary material available at 10.1186/s13063-022-06792-x.

## Administrative information

Note: the numbers in curly brackets in this protocol refer to SPIRIT checklist item numbers. The order of the items has been modified to group similar items (see http://www.equator-network.org/reporting-guidelines/spirit-2013-statement-defining-standard-protocol-items-for-clinical-trials/)

**Table Taba:** 

Title {1}	AGI grade-guided chaiqin chengqi decoction treatment for predicted moderately severe and severe acute pancreatitis (CAP trial): study protocol of a randomised, double-blind, placebo-controlled, parallel-group, pragmatic clinical trial
Trial registration {2a and 2b}.	Chictr.org.cn Registry (ChiCTR2000034325). Registered on 2 July, 2020. https://www.chictr.org.cn/showproj.aspx?proj=55591
Protocol version {3}	The current protocol is version 1, dated December 10, 2019.
Funding {4}	This study is supported by Project of Sichuan Provincial Administration of Traditional Chinese Medicine (Grant No. 2020ZD004) and NZ-China Strategic Research Alliance 2016 Award, Ministry of Science and Technology, China (Grant No. 2016YFE0101800).

## Introduction

### Background and rationale {6a}

Acute pancreatitis (AP) is an inflammatory disorder of the pancreas [1]. The common causes of AP such as gallstones, alcohol, hypertriglyceridaemia, endoscopic retrograde cholangiopancreatography (ERCP), and various drugs trigger self-digestion of acinar cells and induce local and systemic inflammation. It has an increasing prevalence with an overall incidence of over 34 affected cases per 100,000 person-years [2]. Most of the patients are uneventful and recover from mild disease (mild acute pancreatitis, MAP), or pull through local complications or transient organ failure defined as moderately severe acute pancreatitis (MSAP). Approximately 15–20% of patients manifesting persistent organ failure (POF) are defined as severe acute pancreatitis (SAP) [3], which are at risk of multiple organ failure (MOF) and the mortality can be up to 50% [4, 5]. Despite the global socioeconomic burden of disease, currently, there are no specific and effective therapeutic agents available to treat AP [6]. According to published guidelines [7, 8], supportive measures, such as analgesia, fluid therapy, nutritional supplementation, and organ support, remain the primary management modalities for AP patients.

Traditional Chinese medicine (TCM), which contains abundant multiple-target biologically active substances, has been broadly used in many countries and regions. Gastrointestinal dysmotility or dysfunction/failure, one of the common and complex complications in AP [9–11], is widely accepted as an important role in the pathogenesis of systemic inflammation and MOF [12–14]. Most TCM herbal formulas, such as dachengqi decoction [15, 16], qingyi decoction [17, 18], and rhubarb [19, 20], are used as an important “gut-centred” therapeutic strategy in the early treatment of AP [21]. Based on TCM theories, we summarised that the key pathogenesis of SAP-MOF is the invasion of “evil heat” to the organs, and its treatment requires “clearing heat, removing toxin, and purging the bowel” in clinical practice [22, 23]. Systematic reviews and meta-analyses of observational studies and trials with small sample sizes have demonstrated the effectiveness of rhubarb-contained TCM in reducing inflammatory markers, organ failure, local complications, and mortality, albeit the included clinical trials are of low quality [24–26].

Chaiqin chengqi decoction (CQCQD) has been modified from dachengqi decoction and used to treat AP in our hospital for over 30 years [27, 28]. The comprehensive approach integrated by TCM and Western medicine improved clinical outcomes and reduced the mortality of SAP to 19.6% [29]. Our previous studies demonstrated that CQCQD can restore intestinal motility or ameliorate systemic inflammation via the toll-like receptor 4 and inflammasome-mediated pro-inflammatory pathways in AP models [23, 30].

Aiming to restoration or maintenance of gastrointestinal function, the Acute Gastrointestinal Injury (AGI) grade-based algorithm will be used to guide the administration of CQCQD [11]. Our trial protocol, informed consent, and other documents were submitted to the Biomedical Research Ethics Committee (BREC) of West China Hospital of Sichuan University in February 2020. After revisions, ethical approval was obtained on 22 June, 2020. The trial was registered with an identifier (ChiCTR2000034325) at chictr.org.cn on 2 July, 2020.

### Objectives {7}

Owing to the lack of sufficient strength of the current evidence, we designed a randomised, double-blind, placebo-controlled, parallel-group trial to provide high-quality evidence of the efficacy of CQCQD for patients with AP (CAP trial).

### Trial design {8}

This study is a single-centre double-blind, parallel-design, pragmatic, placebo-controlled randomised trial. The study flowchart is shown in Fig. 1. The trial framework is exploratory.

**Fig. 1 Fig1:**
[figure not shown]
Study flowchart. CQCQD, chaiqin chengqi decoction; AGI, acute gastrointestinal injury; BISAP, Bedside Index of Severity in Acute Pancreatitis; GCS: Glasgow Criteria System; IAP: intra-abdominal pressure; QD: once daily; TID: three times a day; Q6H: every 6 h; Q4H: every 4 h; Q2H: every 2 h

The protocol follows the recommendations of Standard Protocol Items: Recommendations for Interventional Trials (SPIRIT) guidelines (Additional file 1) [31, 32]. The Pragmatic Explanatory Continuum Indicator Summary Framework-2 (PRECIS-2) (Additional file 2), a validated tool for decision making and discussion of trial design, was used to help us design this pragmatic trial and judge whether these design decisions were fit for our purpose of designing a pragmatic trial [33]. The Consolidated Standards of Reporting Trials (CONSORT) has been used as frameworks of methodology to design this protocol [34].

## Methods: participants, interventions and outcomes

### Study setting {9}

Patients with AP will be recruited through the Pancreatitis Centre Ward of West China Hospital. Eligible patients will be randomly assigned to the treatment or control group with the ratio of 1:1.

### Eligibility criteria {10}

The CAP trial focuses on eligible patients with predicted MSAP and SAP who are admitted within 72 h of onset. A patient will be considered eligible if he/she meets the inclusion criteria and does not meet any of the exclusion criteria.

#### Inclusion criteria

Patients will be included if they fulfil all the following criteria:Meet the diagnostic criteria of AP [3], which fulfil two of the following three items: typical symptoms and signs of abdominal pain, elevated serum amylase and/or lipase at least three times the upper limit of normal, and AP characteristic image findings.Aged between 18 and 75 years, male or female.Admitted to Pancreatitis Centre Ward within 72 h of disease onset.Written informed consent obtained.

#### Exclusion criteria

Patients with any of the following conditions will be excluded:Known pregnant or lactating at admission.The presence of severe organ failure identified using Sequential Organ Failure Assessment (SOFA) scoring by a score of > 3 for individual organs (respiratory, cardiovascular, or renal systems) at admission [35].The predicted MAP defined as a Harmless Acute Pancreatitis Score (HAPS) > 2 at admission [36].Known malignant tumour or having radiotherapy and chemotherapy within 6 months.Known gastrointestinal perforation, bleeding, and mechanical ileus at admission.Acute attack of chronic pancreatitis.Known history of neoplasm in duodenal or biliopancreatic systems.Known history of pancreatic resection.Known undergoing other clinical trials.Known taking TCM orally before enrolment.

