### Intervention description {11a}

#### Administration of randomised drugs guided by the AGI-based algorithm

The AGI grade has been widely used to assess gastrointestinal injury in patients with acute critical illness [11, 40]. Evidence has shown that the AGI grading system is useful for identifying the severity of gastrointestinal dysfunction/failure in AP [41]. In our study, the participants will receive randomised drugs guided by the AGI-based algorithm (Fig. 1).Initiation: If the Bedside Index of Severity in Acute Pancreatitis (BISAP) score or Glasgow Criteria System (GCS) < 2 at allocation [42, 43], the patients will empirically receive CQCQD or placebo 200 mL oral intake (or intragastric infusion) and enema, 3 times a day. If the patients have a BISAP/GCS score ≥ 2 at allocation, they will be required to receive urethral catheterisation to monitor intra-abdominal pressure (IAP) every 4 h, which is the key index in AGI grade. The dosage and frequency of decoction is determined by AGI grading according to the following criteria: (1) if AGI grade = 1, 200 mL CQCQD or placebo is administered orally (or intragastrical infusion) and enema, 3 times a day; (2) if AGI grade = 2, CQCQD or placebo is given 100 mL orally (or intragastrical infusion) and 200 mL enema, every 6 h; (3) if AGI grade = 3, CQCQD or placebo are given 100 mL orally (or intragastric infusion) and 200 mL enema, every 4 h; (4) if AGI grade = 4, CQCQD or placebo is given 100 mL orally (or intragastric infusion) and 200 mL enema, every 2 h. If the patient with a BISAP/GCS score ≥ 2 at allocation rejects urethral catheterisation, the initial administration of the randomised drug is in accordance with AGI grade 1, and the conditions will be reassessed for further judgement.Continuation: AGI grade is evaluated daily at 7–8 am by the researchers. The dosage and frequency of CQCQD or placebo are determined by the corresponding AGI grade at the time points.Termination: CQCQD or placebo is administered for at least 5 days and no more than 14 days. IAP monitoring will be terminated if it is less than 15 mmHg for two consecutive days. CQCQD or placebo will be terminated, if AGI grade < 1 for two consecutive days, or normally oral refeeding without discomfort. Other conditions will be determined by clinical treatment leaders and principal investigators.The upgrade principle for patients with AGI grade 1 initially or who reject urethral catheterisation: (1) the aggravation of abdominal distension and constipation; (2) the occurrence of new organ dysfunction; (3) the deterioration of the original organ function; and (4) other conditions will be assessed and determined by clinical treatment leaders and principal investigators.

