
### Criteria for discontinuing or modifying allocated interventions {11b}

The patients are withdrawal if they meet any of the following criteria:Having manifestations of gastrointestinal perforation, bleeding, mechanical ileus, severe haemorrhoids, and anal fissure which require restricted fast and enema.Quitting voluntarily.Adverse medical events occurring during the study, such as severe hypernatremia, intolerance to critically worsening conditions, or other reasons as judged by the investigators, which might make the patient unlikely to complete the study.

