### Sample size {14}

The sample size calculation was based on the following assumptions: a reduction in duration of respiratory failure of 2 days in the treatment group, and a standard deviation of 4.5 days for each group [17, 29]. Assuming that the significance level is 0.05 and the study power is 0.8 (two-sided *α* = 0.05, *β* = 0.2), we projected a sample size of 111 patients in each group using Power Analysis & Sample Size software (PASS statistic software, version 11.0.7, NCSS). Considering a 10% dropout rate, a total of 248 patients will be recruited in this trial with 124 patients for each group.

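### Severe haemorrhoids and anal fissure that rule out an enema are grounds for withdrawal but not for exclusion, although every dosing regimen includes an enema

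*Protocol article*

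**What the plan says.** All places are in the protocol article.

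- **Eligibility criteria {10}** makes the lists decisive: "A patient will be considered eligible if he/she meets the inclusion criteria and does not meet any of the exclusion criteria".
- **Exclusion criteria** has one gastrointestinal item: "Known gastrointestinal perforation, bleeding, and mechanical ileus at admission". No other exclusion mentions anorectal disease, a contraindication to enema, or investigator judgement.
- **Criteria for discontinuing or modifying allocated interventions {11b}** opens with "The patients are withdrawal if they meet any of the following criteria". Its first item is "Having manifestations of gastrointestinal perforation, bleeding, mechanical ileus, severe haemorrhoids, and anal fissure which require restricted fast and enema". Its third item begins "Adverse medical events occurring during the study".
- **Intervention description {11a}** gives the dosing rules. For a low severity score at allocation, "the patients will empirically receive CQCQD or placebo 200 mL oral intake (or intragastric infusion) and enema, 3 times a day". At the other end, "if AGI grade = 4, CQCQD or placebo is given 100 mL orally (or intragastric infusion) and 200 mL enema, every 2 h". AGI grades 2 and 3 also combine the oral or intragastric route with an enema. No regimen without an enema is set out.

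**The concern.** The withdrawal list shows that the authors see severe haemorrhoids and anal fissure as a reason to restrict enemas. These conditions can be asked about before consent and randomisation, when acting on them costs least. The exclusion list nevertheless screens for the other three conditions in the same item and leaves these two out.

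At stake is, first, the safety of a patient who enters with such disease. The control is a 10% decoction given by the same routes, so both arms are exposed. Second, the trial may have withdrawals after randomisation that screening could have prevented.

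**Working it through.** The check is mainly a comparison of three lists, with a little counting.

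**1. Conditions in the first withdrawal item against the exclusion list**

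| Condition | Withdrawal item {11b} | Excluded if known at admission |
|---|---|---|
| Gastrointestinal perforation | yes | yes |
| Bleeding | yes | yes |
| Mechanical ileus | yes | yes |
| Severe haemorrhoids | yes | no |
| Anal fissure | yes | no |

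Unmatched: 5 − 3 = 2.

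**2. Distinct regimens and whether they include an enema (Intervention description {11a})**

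| Regimen | Who receives it | Enemas per day |
|---|---|---|
| Grade 1 | AGI grade 1; BISAP/GCS below 2; BISAP/GCS of 2 or more with catheterisation refused | 3 |
| Grade 2 | AGI grade 2 | 24/6 = 4 |
| Grade 3 | AGI grade 3 | 24/4 = 6 |
| Grade 4 | AGI grade 4 | 24/2 = 12 |

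There are six ways into the algorithm but four distinct regimens, and all four include an enema. Treatment lasts at least 5 days, so the lightest schedule held throughout means 3 × 5 = 15 enemas.

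**3. Which patients fall into the gap.** Bleeding haemorrhoids or fissures are arguably covered already by the bleeding exclusion. Disease that does not restrict enema does not meet the withdrawal item. What remains is known, non-bleeding disease that precludes an enema. Such a patient meets no exclusion and is eligible.

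**4. Both readings of the withdrawal item.** The first item has no onset limit, whereas the third is limited to events during the study.

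- If the first item covers disease already present, the patient meets a withdrawal criterion on the day of randomisation.
- If it covers only events on study, disease known at admission is caught by neither list, and the algorithm prescribes an enema.

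The gap exists on either reading.

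**5. Size relative to the sample.** Sample size {14} states: "Considering a 10% dropout rate, a total of 248 patients will be recruited in this trial with 124 patients for each group". The dropout step reproduces: 111/(1 − 0.10) = 123.3, rounded up to 124 per group, and 2 × 124 = 248. The allowance is 248 − 2 × 111 = 26 patients.

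The article gives no prevalence of the two conditions. Purely as an assumption:

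| Assumed prevalence | Patients out of 248 |
|---|---|
| 1% | 248 × 0.01 = 2.5 |
| 2% | 248 × 0.02 = 5.0 |
| 5% | 248 × 0.05 = 12.4 |

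These figures only show scale. They are not estimates.

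**6. Effect on the analysis.** The section on non-adherence and missing data {20c} analyses patients as randomised, whatever treatment they actually took. The section on outcome collection {18a} continues follow-up after the study drug stops unless the participant leaves the trial. A patient taken off the drug but still followed therefore supplies the primary outcome and uses no dropout place. Someone who does not finish the trial leaves the per-protocol set, which keeps only completers.

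**The case against.** Exclusion and discontinuation lists do different jobs and need not match. The heading of {11b} concerns stopping or modifying treatment, which suggests events on study, and enemas as often as every 2 h could plausibly aggravate anorectal disease. That would explain why the two conditions appear there and not among the exclusions. This stands: the mismatch is not a contradiction in terms, and a reader who infers one goes further than the text allows. It does not close the gap, because on that reading known disease at admission is not screened at all.

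Clinical judgement offers partial cover. The withdrawal list allows other reasons as judged by the investigators, and {18a} lets the treating physician stop the drug. A short exclusion list also suits a pragmatic trial with flexible adherence. This softens the safety concern, but both provisions act only after randomisation.

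The affected group is narrow and unquantified, and little recruitment may remain. Both points stand and limit the benefit of a change.

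A reader might infer that each such patient uses up one of the 26 dropout places, or that the primary comparison is biased. The documents support neither. A place is lost only if the patient leaves follow-up, and the analysis is by randomised group irrespective of actual use.

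**Conclusion.** The point holds as an optional improvement. As written, a patient with known, non-bleeding severe haemorrhoids or anal fissure precluding enema is eligible, and every available regimen then prescribes an enema. Two of five conditions lack a matching exclusion, and four of four regimens are affected. The number of patients cannot be derived from the article.

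The consequence is for safety at the first dose and for avoidable withdrawals after randomisation. The effect on the primary intention-to-treat comparison is negligible; some patients may leave the per-protocol set.

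Two assumptions underlie this. The qualifier about restriction in the withdrawal item is loosely worded, and I read it as disease for which an enema has to be withheld. I also take the printed exclusion list as complete, since the eligibility section makes it decisive.

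**What to change.** Add one line to the exclusion criteria: *Known severe haemorrhoids or anal fissure precluding enema at admission.*

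Leave the first withdrawal item as it is. It may be tempting to limit it to onset or worsening after randomisation, but disease that was present, undiagnosed and found only at the first enema would then be covered by neither rule. The present wording, without an onset limit, can cover that patient.

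The cost is a few more screen failures and a protocol amendment, which under section {25} needs ethics committee review and approval, a registry update and notice to participants. Only patients still to be enrolled would benefit. Recruitment began on August 1, 2020, the article appeared on November 8, 2022, and completion is expected in June 2023. If that completion date includes the 26-week follow-up, which is an assumption, enrolment would end in about December 2022 and the amendment might reach few patients or none.

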### Who will take informed consent? {26a}

Before enrolment, consents for this study are obtained from each patient or his/her next of kin with full information regarding the possible adverse effects of the experimental drug and potential consequences. They will be told about the equal chance of allocation to any one of the two groups before signing the informed consent form. Meanwhile, they will be given enough time to decide whether they join the trial or not. At last, patients will be included voluntarily by signing written informed consent by research assistants.

### Additional consent provisions for collection and use of participant data and biological specimens {26b}

On the consent form, participants will be asked whether they agree to the use of their data and biological specimens. Participants will also be asked to consent to the research team sharing relevant data with regulatory authorities, as appropriate. No identifying images or other personal or clinical details of participants are presented here or will be presented in reports of the trial results. Informed consent forms are available, on request, from the corresponding authors.

